**List of Abbreviations**

PI- Principal Investigator

SAE- Serious Adverse Event

API- Active Pharmaceutical Ingredient

CHPS- Center for Human Phonemic Science (Formerly CTRC- Clinical Translational Research Center)

## Study Summary

|                                       |                                                                                                                                                                                                                                                |
|---------------------------------------|------------------------------------------------------------------------------------------------------------------------------------------------------------------------------------------------------------------------------------------------|
| Title                                 | INTRAOPERATIVE MOLECULAR IMAGING OF PULMONARY NODULES BY SGM-101, A FLUOROCHROME-LABELED ANTI-CARCINO-EMBRYONIC ANTIGEN (CEA) MONOCLONAL ANTIBODY                                                                                              |
| Short Title                           | Intraoperative Imaging of Pulmonary Nodules by SGM-101                                                                                                                                                                                         |
| Protocol Number                       | xxxxx                                                                                                                                                                                                                                          |
| Phase                                 | Pilot and exploratory                                                                                                                                                                                                                          |
| Methodology                           | Open Label                                                                                                                                                                                                                                     |
| Study Duration                        | 24 Months                                                                                                                                                                                                                                      |
| Study Center(s)                       | Single Center                                                                                                                                                                                                                                  |
| Primary Objective                     | The primary end-point of the study is to determine the sensitivity of SGM-101 in identifying lung nodules when excited by a near-infrared light source.                                                                                        |
| Secondary Objective                   | The secondary objective is to measure the concordance of fluorescence and tumor type.                                                                                                                                                          |
| Number of Subjects                    | We intend to enroll 20 lung cancer subjects in this study.                                                                                                                                                                                     |
| Diagnosis and Main Inclusion Criteria | The study is focusing on subjects presenting with suspected malignancies of the lung and pleura who are considered to be good surgical candidates.                                                                                             |
| Study Product, Dose, Route, Regimen   | SGM-101 is a fluorescent conjugate comprised of a tumor-specific, anti-carcinoembryonic antigen (CEA) monoclonal antibody and a near infrared (NIR) emitting fluorochrome. We will give 5 to 10 mg intravenously 3 to 5 days prior to surgery. |
| Duration of administration            | The proposed dose of SGM-101 to be investigated in this study is 10 mg to be administered intravenously over 30-60 minutes.                                                                                                                    |
| Reference                             | Non-placebo controlled                                                                                                                                                                                                                         |
| Statistical Methodology               | The sensitivity and specificity of the intra-operative imaging will be estimated using microscopic pathological examination as the gold standard. Exact 95% confidence intervals will be generated around these estimates.                     |

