### 3 Study Design

#### 3.1 General Design

Subjects will be seen in a General Thoracic Surgery clinic. If they have a lung nodule that is suspicious for a lung non-small cell lung cancer, they will be a candidate for the operation. From our prior experience, we have an 90% positive predictive value based on CAT and PET scans that a subject with a suspected lung cancer will in fact have lung cancer. The subjects with lung and pleural nodules will be prospectively consented to participate in this trial. There will be no randomization or control group and only subjects previously scheduled to undergo surgery will be eligible to participate. We anticipate a 24-month period will be necessary to reach our accrual goal of 20 subjects.

After obtaining informed consent, subjects will receive a one-time dose of 5 to 10 mg of SGM-101, up to 5 days prior to the planned operation. As a prophylactic measure, we may recommend giving 25 mg of IV Benadryl to the subject prior to the infusion of SGM-101 to ensure possibility of allergic reaction is absolutely minimized. This will be at the discretion of the principal investigator. The goal of surgery in subjects is to remove the nodule and lymph nodes in concern. During surgery, we will take images with an intra-operative camera system. Imaging will take place prior to surgical resection to record the localization of tumors, and post-resection to document the visualization of any residual tumor. All documenting of nodules will take place in an electronic report form.

Our analysis will be the following:

| Data Analysis of a Diagnostic Test |                    | Test result                                        |                                                   | Data Analysis                                                             |
|------------------------------------|--------------------|----------------------------------------------------|---------------------------------------------------|---------------------------------------------------------------------------|
|                                    |                    | True
(accept $H_0$ )                            | False
(accept $H_A$ )                          |                                                                           |

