### 5.2 Treatment Regimen

The proposed dose of SGM-101 to be explored in this study is 5-10 mg to be administered intravenously over 30 minutes followed by a 50 mL flush of isotonic saline to account for the dead volume of the tubing. SGM-101 will be administered 3 to 5 days (+/-1 day) prior to surgery..

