## 6.2 Visit 2- CHPS (infusion up to 5 days before surgery)

Visit two will consist of the infusion of SGM-101 and surgery. Based on the discretion of the surgeon, 25 mg of Benadryl may or may not be administered prior to infusion of study drug. Once the administration of the Benadryl, is completed, the drug will be administered by the surgeon or CHPS personnel. Note that SGM-101 should not be mixed with other medicinal products and should not be given simultaneously through the same intravenous line as another medicine. During this time, the subject will be monitored by CHPS personnel for signs of an allergic reaction. Vital signs (Heart rate, Blood Pressure, Pulse/Oxygen levels, body temperature and skin color) will first be collected and recorded at pre-infusion, next at 15-minute intervals after the infusion has begun up until the 45-minute infusion is complete (see chart below). This will include the 30 minutes for the infusion of the drug and the 15 minutes for the infusion of the flush.

|            | Pre-Infusion | Infusion Start | 15 minutes after starting infusion | 30 minutes after starting infusion; end of infusion | 45 minutes after starting infusion | 60 minutes after starting infusion |
|------------|--------------|----------------|------------------------------------|-----------------------------------------------------|------------------------------------|------------------------------------|
| Time       |              |                |                                    |                                                     |                                    |                                    |
| Temp       |              |                |                                    |                                                     |                                    |                                    |
| HR         |              |                |                                    |                                                     |                                    |                                    |
| BP         |              |                |                                    |                                                     |                                    |                                    |
| O2 Sat     |              |                |                                    |                                                     |                                    |                                    |

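### The protocol gives conflicting statements of dose, dosing-to-surgery interval, drug infusion time and vital-sign schedule, so the one pooled sensitivity could mix regimens

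*Protocol*

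**What the plan says.** **Dose.** The Study Summary's regimen row reads "We will give 5 to 10 mg intravenously 3 to 5 days prior to surgery". Its next row, on duration of administration, reads "The proposed dose of SGM-101 to be investigated in this study is 10 mg to be administered intravenously over 30-60 minutes". Section 3.1 has "subjects will receive a one-time dose of 5 to 10 mg of SGM-101, up to 5 days prior to the planned operation", and section 5.2 has "The proposed dose of SGM-101 to be explored in this study is 5-10 mg to be administered intravenously over 30 minutes". Section 5.3 states that there is a single treatment group. No section says how a subject's dose within the range is chosen.

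**Interval.** The Summary gives 3 to 5 days. Sections 3.1 and 6.2 set only an upper limit; the heading of 6.2 says "infusion up to 5 days before surgery". Section 5.2 says "SGM-101 will be administered 3 to 5 days (+/-1 day) prior to surgery". The opening sentence of 6.2 puts both infusion and surgery in Visit 2, whereas the Schedule of Procedures gives them separate visits (2 and 3).

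**Infusion time.** The Summary allows 30-60 minutes. Section 5.2 gives 30 minutes and then a flush. Section 6.2 also allots 30 minutes to the drug and adds 15 minutes for the flush.

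**Vital signs.** After the pre-infusion reading, the text of 6.2 schedules them "next at 15-minute intervals after the infusion has begun up until the 45-minute infusion is complete". The chart below that text has a further column at 60 minutes.

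**Analysis.** Sections 7.1 and 7.2 use one nodule per patient and a denominator of 20 for the whole study. The protocol gives no breakdown by dose or interval.

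**The concern.** These are operating instructions in the current text. Staff working from different sections would dose, time and monitor subjects differently, and could not tell what counts as a deviation: an infusion six days before surgery complies with 5.2 and breaches the Summary, 3.1 and 6.2.

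The statistical stake is the meaning of the main estimate. In section 1.4 the earlier colorectal and pancreatic study is reported by dose level and by days before surgery, with results that differed on both. If the 20 lung subjects receive different doses at different intervals, the pooled sensitivity is an average over a mix that the protocol does not fix. A disappointing value could then reflect the agent, the dose or the timing.

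The safety stake is narrower and conditional. The readings in 6.2 accompany observation for allergic reaction, and section 1.2 says serum concentration usually peaks at or near the end of infusion. A schedule built for the shorter infusion would miss the period after that point if the longer one were used.

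**Working it through.** **Interval.** Applying the tolerance in 5.2: 3 - 1 = 2 days and 5 + 1 = 6 days. Read literally, the sections compare as follows.

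| Days from infusion to surgery | Summary (3-5) | 3.1 and 6.2 heading (at most 5) | 5.2 (2-6) |
|---|---|---|---|
| under 2 | no | yes | no |
| 2 | no | yes | yes |
| 3 to 5 | yes | yes | yes |
| 6 | no | no | yes |

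All the statements agree only on days 3 to 5.

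**Infusion and vital signs.** The protocol's own total reproduces: 30 min drug + 15 min flush = 45 min (6.2). This agrees with 5.2, so the only conflict on infusion time is with the Summary's 30-60 minutes. Take the last reading as 45 min (text) or 60 min (chart), keep the flush at 15 min, and subtract the end of drug and the end of flush. A negative number means that readings stop too early.

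| Drug infusion | Drug ends | Flush ends | Text: 45 minus drug end / flush end | Chart: 60 minus drug end / flush end |
|---|---|---|---|---|
| 30 min | 30 | 45 | +15 / 0 | +30 / +15 |
| 45 min | 45 | 60 | 0 / -15 | +15 / 0 |
| 60 min | 60 | 75 | -15 / -30 | 0 / -15 |

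Both schedules cover a 30-minute infusion. At 60 minutes, the text stops 15 minutes before drug ends and the chart stops as it ends.

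**Pooling.** If a share w of the cancers is imaged under a regimen with sensitivity s1 and the rest under one with s2, the pooled value is w × s1 + (1 - w) × s2. The protocol gives no regimen-specific sensitivities for lung, so the following values are assumptions that only show the mechanism.

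- s1 = 40%, s2 = 80%: the pooled value is 80% at w = 0, 60% at w = 0.5 and 40% at w = 1.
- s1 = 50%, s2 = 70%: the pooled value is 70%, 60% and 50% at the same shares.

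A pooled 60% is therefore compatible with either pair at an equal mix, or with 60% under every regimen. The pooled figure alone cannot separate these cases.

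**The case against.** The strongest reply is that this is a pilot with mainly descriptive analyses, that 5.2 presents the dose range as something to explore, and that 2 to 6 days matches the range used in the earlier study. A single treatment group means that there are no separate arms; it does not contradict a dose range. If every subject in fact receives one dose at one interval, the pooled estimate describes that regimen. All of this stands. It rules out calling the estimate uninterpretable, or saying that it describes no regimen. It does not reconcile the sections.

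Four stronger readings are tempting, and the protocol does not support them.

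- *The 45 minutes in 6.2 is a third infusion time.* It is drug plus flush, and it agrees with 5.2.
- *Monitoring ends too early.* This holds only if the Summary's longer infusion is used. Under 5.2 and 6.2, readings continue 15 minutes (text) or 30 minutes (chart) past the end of drug.
- *Same-day dosing is allowed.* A reader might infer it from the missing lower limit and the opening of 6.2. The Schedule of Procedures, the heading of 6.2 and the separate surgery section 6.3 point to a drafting slip.
- *Serum half-life measures the damage.* With the mean of about 30 h in section 1.2, 2^(-48/30) = 0.330 remains at day 2 and 2^(-144/30) = 0.036 at day 6, about a 9-fold difference. But these are preliminary serum data from another population. At day 4 the fraction is 2^(-96/30) = 0.109, a third of the day 2 level, yet section 1.4 reports day 4 as the most favorable. It also reports that a higher dose did not always raise the tumor-to-background ratio. Serum decay therefore does not predict tumor fluorescence.

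The case report form, the nurse flow sheet and any statistical analysis plan are not shown. They may already capture dose and times, or plan a listing by regimen, so their absence is not part of this point.

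**Conclusion.** The point holds as an internal contradiction on four items: dose, interval, drug infusion time and vital-sign schedule. It is more than clerical, because each version leads to different conduct.

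The definite sizes are a two-fold range of dose with no allocation rule, days 2 and 6 each allowed in some sections and excluded in others, and a 15-minute difference between the text and chart of 6.2. The monitoring shortfall of 15 minutes (text) or 0 minutes (chart) relative to the end of drug depends on a 60-minute infusion being used.

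The effect on the pooled sensitivity is a possibility of unknown size. It rests on two assumptions: that subjects actually receive differing regimens, and that the dependence on dose and interval reported in colorectal and pancreatic cancer carries over to lung. That evidence is itself limited, since section 1.4 acknowledges unequal dose groups and a sub-optimally powered comparison.

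**What to change.** The sponsor should reconcile the Study Summary with sections 3.1, 5.2 and 6.2, so that one dose statement, one interval with any tolerance included, one drug infusion time and one vital-sign schedule apply throughout. The opening sentence of 6.2 should be brought into line with the Schedule of Procedures. The values are for the sponsor to choose; this review does not favor any of them.

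If a range of doses or intervals is kept, the protocol should say how a subject's dose is chosen. Each subject's actual dose, time from infusion to imaging and fluorescence result should then be listed descriptively beside the pooled estimate.

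The cost is amendment wording and one small listing. With 20 subjects the listing cannot formally separate dose from interval effects. It only lets a reader see whether regimens were mixed, and whether missed tumors cluster in one of them.

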## Schedule of Procedures

| Study Procedure                                                                                    | Visit 1
Screening | Visit 2
Infusion
Day | Visit 3
Surgery
Day | Visit 4
Post-
Operative
F/up |
|----------------------------------------------------------------------------------------------------|-----------------------------|-----------------------------------|----------------------------------|----------------------------------------------|
| Informed consent                                                                                   | X                           |                                   |                                  |                                              |
| Inclusion/exclusion
criteria met                                                                | X                           |                                   |                                  |                                              |
| Lung, pleural
nodule or mass
presumed to be
resectable on pre-
operative
assessment | X                           |                                   |                                  |                                              |
| Medical history                                                                                    | X                           |                                   |                                  |                                              |
| Serum or urine
pregnancy test for
childbearing
women                                      |                             | X                                 |                                  |                                              |
| Vital signs (Temp,
HR, BP, Pulse/Ox,
Skin Color)                                             |                             | X                                 |                                  |                                              |
| Study drug
administration                                                                       |                             | X                                 |                                  |                                              |
| Surgery with
associated
procedures
including intra-
operative imaging                  |                             |                                   | X                                |                                              |
| AE assessments                                                                                     |                             | X                                 | X                                | X                                            |
| ADE assessments                                                                                    |                             | X                                 | X                                | X                                            |

## 1 Introduction

This document is a protocol for a human research study. This study is to be conducted according to US and international standards of Good Clinical Practice (FDA Title 21 part 312 and International Conference on Harmonization guidelines), applicable government regulations and Institutional research policies and procedures.

### 1.1 Background

According to the World Health Organization, lung cancer is the most common cause of cancer-related death in men and women, and is responsible for 1.5 million deaths worldwide annually as of 2017. Surgery remains the best option for subjects presenting with operable Stage I or II cancers, however the five-year survival rate for these candidates remains at a dismal 73% for Stage I and 53% for Stage II (1). The high rates of local recurrence suggest that surgeons are unable to completely detect and remove primary tumor nodules in a satisfactory manner as well as lingering metastases in sentinel lymph nodes. By ensuring a negative margin through imaging during surgery it would be possible for us to improve the rates of recurrence free subjects and thus overall survival.

Over the last several years, our group has taken a novel approach to the surgical approach (2-5). Specifically, we have started injecting contrast agents that go selectively to tumors and allow them to fluoresce. We postulate that provides an additional tool in the operating room for surgeons to find tumors and their margins.

Thoracic malignancies are the ideal disease to investigate intra-operative imaging. Over 25-65% of lung and pleural malignancies express carcinoembryonic antigen (CEA), therefore making CEA a target for imaging agents (6-11). Interestingly, there is minimal expression of CEA in normal lung, therefore, the background to noise of CEA in cancers versus normal lung is very high. Unfortunately, unlike colorectal cancer, it is not evident that serum CEA levels correlate with lung cancer, specifically non-small cell lung cancer.

CEA is a glycoprotein product of the gene CEACAM-5 and is a member of the immunoglobulin superfamily that serves as a cell-adhesion molecule and may also have an effect on innate immunity. High serum CEA levels have been identified as a prognostic factor in both resected NSCLC and in metastatic disease (6, 7, 11-13).

CEA has previously been considered a promising target for monoclonal antibodies to be used in radio-immunodiagnostic and radio-immunotherapy, and over a hundred clinical studies involving a number of different anti-CEA antibodies have been conducted in this field (14, 15). The radiolabeled anti-CEA antibody CEA-Scan (arcitumomab) from Immunomedics GmbH was authorized in the European Union in 1996 and in the United States in 1999 to assess recurrent or metastatic disease in patients with colorectal cancer. The product has since been withdrawn from the market for commercial reasons but it is important to mention that during its 9 years of use, no adverse effects have been reported.

